#### Freedom of choice, choice overload, and values

Choices are usually considered on a continuum from totally uninfluenced to the ones molded by formal and informal social norms. While norms play an important role in vaccination decisions (Gust et al., 2008; Brunson, 2013a,b), how we perceive those norms and how we perceive freedom when making the choice also influence the decision. This subjective perceived freedom is associated with choice overload in decision making processes (Lau et al., 2015). Decisions and decision-making processes can be exhausting and overwhelming, hence decision makers can find it difficult to retain all the necessary information needed to make an informed decision. We expect parents who experience lower levels of perceived freedom to have a higher tendency to adhere to perceived social norms. We also expect those individuals to be more likely to conform to authorities and to other stakeholders (health professionals, government etc.).

According to the cultural cognition of risk (Kahan and Braman, 2006; Kahan et al., 2010), the evaluation of riskiness is in line with values that we share as a culture. The operationalization of values regarding vaccination is a challenge, therefore we decided to use an indirect measure instead. We will measure participants' actively open-minded thinking style, a construct which was found to predict the tendency to acquire information in order to make competent decisions (Haran et al., 2013; Baron et al., 2015). We expect individuals who are more open-minded to be more likely to seek information from both sides of vaccine hesitancy spectrum (more diverse sources), be less affected by social norms, and show less vaccine hesitancy. The diversity in the sources of information will be rated by the proportion of official and informal sources.

#### Perception of danger

Threat perception has been widely used to encourage health-related actions such as vaccinations, but messages that increase risk perceptions are less effective than those increasing perceived effectiveness (Ruiter et al., 2001, 2014). However, parents are more likely to vaccinate or intend to vaccinate their children if they perceive the danger of not vaccinating (e.g., perceived vulnerability of their child contracting a certain disease) as high (Seeman et al., 2010; Healy and Pickering, 2011; Jolley and Douglas, 2014; Highland, 2016).

Health-related decisions often comprise of high levels of uncertainty and varying degrees of potential risk. Given that health professionals and other experts differ vastly in coping with uncertainty and risk taking (Grol et al., 1990), it is not surprising that parents are also under great strain when deciding. As stated before, parents often perceive vaccinating their children more risky than not vaccinating them, and as willingness to take risks is associated with making obligatory medical decisions (Grol et al., 1990), we expect to find the same connection in parents, with those less willing to take risks to be more vaccine hesitant.

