##### Passive risk-taking

We will measure participants' tendency of passive risk-taking using the Passive Risk-Taking Scale (Keinan and Bereby-Meyer, 2012). While risk mostly occurs during action, passive risk-taking can influence potential losses due to inaction. This test contains three subscales regarding risks that involve resources, medical issues and ethical issues. It has 25 items in total and uses a Likert-type rating scale in which participants will rate how likely they will act according to the statements (i.e., “Get vaccinated for the flu in the winter”). This scale has a high internal validity and reliability (α = 0.82).

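### The Study 1 risk hypothesis is about the risk of acting, but the scale named to test it measures risk through inaction, so for vaccination content the two point in opposite directions

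*Protocol article*

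**What the plan says.** Under Perception of danger, Study 1 states the premise that "parents often perceive vaccinating their children more risky than not vaccinating them". It links willingness to take risks to making obligatory medical decisions and predicts "those less willing to take risks to be more vaccine hesitant".

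Under Passive risk-taking, the article names the instrument: "We will measure participants' tendency of passive risk-taking using the Passive Risk-Taking Scale". It sets this construct apart from ordinary risk: "While risk mostly occurs during action, passive risk-taking can influence potential losses due to inaction". The scale has 25 items in three subscales (resources, medical, ethical) and a stated alpha of 0.82. Respondents rate how likely they are to do what each statement describes, and the one example given is "Get vaccinated for the flu in the winter".

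Under Proposed analysis, the construct appears only as risk taking, without a direction. It is one of the decision constructs that enter a factor analysis in each country. The resulting factors predict intention to vaccinate, and the same variables also enter a multivariate analysis of variance by level of adherence to the schedule. The criterion, under Intention to vaccinate, is a single item on vaccinating one's child by the official schedule.

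**The concern.** The prediction needs a measure of willingness to accept the risk of doing something: if vaccinating feels like the gamble, parents who avoid gambles hold back. The named scale measures willingness to accept the risk of not doing something. A parent who avoids that kind of risk is one who acts, and in the scale's own example acting means being vaccinated.

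What is at stake is the reading of the result. If passive risk-taking goes with more hesitancy, which is what the vaccination content of the scale favours, the stated hypothesis would count that as evidence against it. The opposite pattern would count as support. In either case a conclusion about willingness to take active risks would be drawn from a scale that does not measure it, and the misreading would recur in each country's separate analysis.

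A smaller matter is that a vaccination item sits inside a score used to explain vaccination outcomes.

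**Working it through.** **Planning figure.** The stated minimum of 222 per country is reproduced by the overall F test in multiple regression with effect size 0.15 (read as f²) and 20 predictors, if alpha 0.05 and power 0.95 are assumed (power at 222 is 0.951). This point does not touch the sample size.

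**Direction.** Setting the sections side by side:

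- *Hypothesis (Perception of danger).* The risky act is vaccinating. Low willingness to take risks should go with high hesitancy.
- *Measure (Passive risk-taking).* The risk lies in inaction. On the flu item, not being vaccinated is the risky response. Low passive risk-taking should go with being vaccinated, that is, with low hesitancy.
- *Coding.* The scoring direction is not stated, but it does not affect this step. Whether a high score means risky or cautious, the cautious respondent on the flu item is the one who vaccinates. The mismatch lies in the construct.
- *Support within the article.* Perception of danger also says that parents who see a high danger in not vaccinating are more likely to vaccinate. That is the direction to expect for risk through inaction.
- *Other measures.* Elaboration of potential outcomes is said to touch attitudes toward risk-taking, but its three subscales are generation/evaluation, positive outcome focus and negative outcome focus. None measures willingness to take an active risk.

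**Limit of this reasoning.** It holds for vaccination content and plausibly for the medical subscale. The article gives no link between vaccination and inaction over resources or ethics, so the sign of the 25-item total remains open.

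**Size of the flu-item overlap.** Inputs from the article: alpha = 0.82, k = 25. Assumptions: equal standardised items; an item-outcome correlation of 0.3 to 0.5; no correlation of the other items with the outcome.

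- Mean inter-item r = alpha / (k − (k − 1) × alpha) = 0.82 / (25 − 24 × 0.82) = 0.82 / 5.32 = 0.154.
- SD of the sum = √(k + k(k − 1) × r) = √(25 + 600 × 0.154) = 10.84.
- Correlation added to the total score = item r / SD: 0.3 / 10.84 = 0.028 and 0.5 / 10.84 = 0.046. Even an item r of 0.9 gives 0.083.
- If a medical subscale of eight items were used (length assumed, not given), the SD is √(8 + 56 × 0.154) = 4.08, and the added correlation is 0.074 to 0.123.

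**The case against.** Several points on the other side are sound.

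- A reader might infer that the sign of the risk coefficient is simply reversed. The documents do not support that. The scoring and full battery are in an appendix that is not shown, and one example item cannot fix the sign of a 25-item total with resource and ethical content.
- The decision matrix in Table 1 does not settle the sign either. It marks not vaccinating as high risk in two of three states, but the hypothesis rests on perceived risk, and hesitant parents may believe in the third state.
- A reader might infer that the flu item repeats the criterion. It does not. As quoted, it reads as the respondent's own seasonal vaccination, while the criterion is the child's official schedule. This is content overlap, and it is small in the total score. An item in the general vaccination scale, on planning to vaccinate one's children, lies much closer to the criterion, so dropping the flu item would not remove criterion overlap from the predictor set.
- In the regression the risk score enters through factors, so no separate risk coefficient is described there. The hypothesis is also stated for hesitancy, while the regression criterion is intention.
- The first pilot is meant to eliminate invalid items.

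None of this removes the mismatch. The risk score still enters the comparison by adherence level as a variable in its own right, and any factor carrying it has to be interpreted. The pilot can screen items but cannot change what the hypothesis says. Nor is this detail left to a fuller plan: the article states both the hypothesis and the instrument, and they refer to different risks.

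**Conclusion.** The concern holds in limited form. The stated hypothesis is about the risk of acting and the named scale is about the risk of not acting. For vaccination content, and plausibly for medical content, the expected associations with hesitancy run in opposite directions. This rests on the article's own description of the construct and its example item, and not on any assumption about scoring. The direction for the full score is undetermined.

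The flu item is a secondary issue of content overlap: about 0.03 to 0.05 in correlation for the total score under the assumed item-outcome correlation of 0.3 to 0.5, and about 0.07 to 0.12 in an assumed eight-item subscale. The correction should be made because, as written, an association between passive risk-taking and hesitancy would be read against the hypothesis.

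**What to change.** Reconcile Perception of danger, Passive risk-taking and Proposed analysis in Study 1:

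- Name passive risk-taking as the construct wherever risk taking is now written, and state which end of the score means more risk.
- Restate the hypothesis for that construct: higher passive risk-taking is expected with higher hesitancy and lower intention, primarily for the medical subscale. Draw no conclusion about willingness to take active risks from this scale.
- Compute the risk score without the flu-vaccination item, at least as a sensitivity check, in models of intention, hesitancy or adherence.

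The cost is a sentence or two of text and one scoring line, with no new data and no change to the sample size. The drawback is that one score is an item shorter than the published scale (24 instead of 25), so it is slightly less comparable with other uses of it.

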#### Access to information

Perception of threat is mediated by access to information. Betsch et al. (2010) found that access to anti-vaccine sources of information increases perceived risks of vaccination. Furthermore, based on their risk perception, different parents trust different kinds of vaccine-related messages. Risk-oriented parents tend to favor statistical over anecdotal arguments, but those who are health-oriented tend to prefer the latter (Downs et al., 2008).

Moreover, knowledge has been identified as an important factor in shaping parents' decisions (Zingg and Siegrist, 2012). A higher number of sources of information has been related to a higher perceived level of knowledge in the frame of decision-making about vaccination (Downs et al., 2008; Rachiotis et al., 2010; Healy and Pickering, 2011; Brunson, 2013a), but the sources of their information can sometimes be problematic. Many parents reported seeking additional information, with most preferring to use the internet rather than consulting a doctor, and would use a general search engine instead of an official or medical website (Downs et al., 2008). Some parents were even found to reserve the decision to vaccinate until enough information was available to them (Highland, 2016). We expect participants who think they have enough access to information to be more likely to score on the extreme ends of the vaccine-hesitant spectrum (i.e., either very pro- or anti-vaccine), and those who are more exposed to anecdotal cases to be more vaccine hesitant. Additionally, in line with previous studies (Rachiotis et al., 2010; Jones et al., 2012; Brunson, 2013b) we expect the type of sources consulted (Official vs. Informal) to predict intention of vaccinate. Anecdotal cases (especially personal experiences) are one of the key forms of communication on the topic of vaccination, particularly among vaccine hesitant groups. This was supported by theoretical models such as the Cultural Attraction theory (Miton and Mercier, 2015), or the Fuzzy-Trace theory (Reyna and Brainerd, 1992; Reyna, 2008). Even vaccine concerns endorsed by a small but vocal group of individuals can heighten vaccine hesitancy in the community (Gowda and Dempsey, 2013). With vaccination being counter-intuitive in its nature (injecting antigens in an already healthy organism to remain healthy), anecdotal cases tap into our intuitive cognitive mechanisms, making individuals less likely to vaccinate. We expect parents that have been exposed to anecdotal cases of bad reactions to vaccines to show higher levels of vaccine hesitancy. However, as mentioned before, Risk vs. Health-orientation can moderate the effect of exposure to anecdotal cases (Downs et al., 2008). For that reason, we expect parents with a negative outcome focus to be more likely to be affetcted by the exposure to anecdotal cases.

### Methods

#### Design, sample, and procedure

Participants will be parents or primary caregivers of children that are of the recommended age to receive vaccinations from their corresponding countries across Europe and Asia (i.e., Finland, Germany, Hong Kong, the Netherlands, Serbia, Slovenia, and Spain). Participants must be (a) over 18 years old, and (b) a parent or care taker of at least one child under the age of 12 years (Salmon et al., 2005; Jones et al., 2012).

The sample size will be a minimum of 222 participants per country, based on a power analysis for an effect size of 0.15, and 20 predictors in a linear multiple regression model. The final sample size will not have a difference greater than 10% between each country. To make sure that there aren't any significant differences between the sample sizes of the different countries, if the sample of any country exceeds 10% of the mean, some participants will be randomly discarded until the criterion is met.

The questionnaire is programmed in JavaScript and will be administered online. To take part in the study, participants will need an electronic device with access to internet. The link with an unbiased invitation letter will be posted on different social media platforms, forums and websites, targeting a wide range of parents from the entire vaccine-hesitancy spectrum. Once the link is opened, participants will first be given a brief introduction of the study. Participants will then read and sign an informed consent, which states they are able to halt and withdraw from the study at any moment without providing a reason, and that they agree for their anonymized data to be analyzed for future publications. Participants will be asked to compose a unique identification code (consisting of their parents' initials, and month of birth), which will be used to identify their data if they decide to withdraw their data after completing the study. After that, participants will be asked to provide their demographic information and complete a battery of vaccination- and decision-making-related questions, with a total of 115 items (the complete battery is in Appendix 1). Participants will be able to leave items unanswered. The study will take ~25 min to complete, but will vary depending on participants' speed of responding. This procedure was ethically approved by the Institutional Review Board of the Faculty of Philosophy at the University of Belgrade.

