### Proposed analysis

We will use statistical software (Matlab, R) for data analysis. We will analyse samples from each country separately because the differences in terms of language, legal framework in relation to vaccines, demographical characteristics and representativeness make the comparability between the different samples, and thus, their conjugate analysis, difficult (Ember et al., 1998).

For each sample, a factor analysis will be conducted to reduce the number of factors and control for interrelatedness of the variables. Two clusters of variables will be included: demographics (age, education level, number of children, mean age of children), and vaccine-related decision constructs (scores on scales on vaccination, vaccine hesitancy, perceived freedom of the decision, choice overload, actively open-minded thinking, trust toward authorities, availability of relevant information, perceived scientific consensus on vaccination, subjective estimation of percentage of children vaccinated on the country, perceived social consensus on vaccination, risk taking, and elaboration of potential outcomes). We expect the factor structure of each sample to be similar. With the reduced number of factors, a multivariate linear regression analysis will be conducted and the predictive power will be tested. The aforementioned factors will serve as predictors, and the parental intention to vaccinate (“I plan to vaccinate my child in accordance to the official vaccination schedule of my country”) will serve as criterion. All variables mentioned will also be included in a multivariate analysis of variance to see if there are differences between them depending on the level of adherence (total adherence, not completely total adherence, no adherence at all) to the official vaccination schedule of their children. We will test the proposed model of mediation (Figure 1) using regression analysis and compare it to a more complicated model with involvement as an additional factor.

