**Figure 1 F1:**
[figure not shown]
Proposed model of the factors of the intention to vaccinate.

For the open-ended question in which parents will detail their reasons for not absolutely adhering to the official vaccination schedule in their country, we will perform a qualitative analysis. After a pre-analysis, we will categorize answers based on the main reasons provided (e.g., medical reasons, considering vaccination risky etc.), and report the frequencies for each of them.

We will also check, using ANOVA, if there are differences in dependent variable (i.e., intention to vaccinate) according to participants' gender, marital status, while also considering whether vaccination is mandatory in their country of residence.

To check if the sources of information parents use to make vaccine-related decisions affect their intention to vaccinate, we will use ANOVA and *post-hoc* analysis.

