### Anticipated results

The samples of this study will consist of data obtained in eight separate countries. This presents both challenges and possibilities. As some of the factors underlying vaccine hesitancy are context-specific and vary across time and place (Dubé et al., 2014), research in multiple countries is needed to understand vaccine hesitancy more fully on a local level. By analyzing our samples separately, we expect the study to contribute to knowledge on locally relevant factors related to vaccine hesitancy. However, the samples are unlikely to be representative in their respective countries, which limits the reliability of out conclusions on local, but not so much on the general level. Special care will also be taken to make sure that we sample people from all parts of the vaccine-hesitancy spectrum; the call for participants will be posted in different interest groups online along with general population call.

Given the sensitive nature of the topic, it is possible for the participants who participate in the study to have stronger convictions toward vaccines in one way or another, which might further decrease the representativeness of the vaccine hesitancy continuum—we want to include parents with various degrees of their hesitancy and strength of their convictions in order to avoid bipolarization. To decrease the effect of the topic on the motivation to participate, all the communication (e.g., invites, instructions) will be neutral in terms of referencing to potential harms and benefits of vaccination as well as any moral judgements of the decision.

Due to the wide range of phenomena of the present study, we hypothesize to find the following factors to reinforce the intent to vaccinate one's child: trust toward authorities, perceived social and scientific consensus, availability of relevant information, along with previously identified demographic characteristics and open-minded thinking. At the same time, we expect to confirm that vaccine hesitancy, perceived freedom, choice overload, the use of informal sources and susceptibility outcome bias serve as reinforces of delaying or omitting mandatory childhood vaccination. All our hypothesized connections can be seen in Figure 1.

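### Randomly discarding respondents from larger countries costs precision, does nothing for the separate per-country analyses, and does not guarantee the stated 10% limit between countries

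*Protocol article*

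**What the plan says.** The Protocol article, Study 1, Design, sample, and procedure, sets three conditions on sample size:

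- A floor: "The sample size will be a minimum of 222 participants per country". It comes from a power calculation for a regression with 20 predictors and an assumed effect size of 0.15.
- A balance criterion: "The final sample size will not have a difference greater than 10% between each country".
- A mechanism: "if the sample of any country exceeds 10% of the mean, some participants will be randomly discarded until the criterion is met".

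The only reason given for the last two is to avoid differences in sample size between countries. The text does not say whether the mean is fixed before trimming or updated as records are removed.

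Study 1, Proposed analysis, then states: "We will analyse samples from each country separately". It justifies this by differences that make joint analysis difficult. Anticipated results repeats it: "By analyzing our samples separately, we expect the study to contribute to knowledge on locally relevant factors related to vaccine hesitancy". One later item in Proposed analysis, an ANOVA of intention by gender and marital status, is to be run "while also considering whether vaccination is mandatory in their country of residence".

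**The concern.** A regression, factor analysis or MANOVA fitted within one country does not depend on how many people answered elsewhere. For those analyses, removing valid questionnaires only makes estimates less precise and makes the result depend on which respondents the draw removed. Small groups shrink in proportion, including parents who do not follow the schedule at all, one of the three adherence levels to be compared.

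The criterion and the mechanism also differ. The criterion is pairwise between countries. The mechanism is one-sided and relative to the mean, and cutting large samples on that trigger does nothing about one small sample. The plan could therefore pay the cost of discarding without reaching the balance it wants.

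**Working it through.** **Inputs.** From the protocol: minimum 222 per country, effect size 0.15, 20 predictors, the 10% limit between countries, and the 10% trigger relative to the mean. Design, sample, and procedure names seven countries and Anticipated results speaks of eight; seven are used here, with eight where it matters. Assumed: the country sizes below (the article gives no expected recruitment), and alpha 0.05 with power 0.95, which are not stated. Taken literally, the trigger would catch almost any sample, so it is read as more than 10% above the mean.

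**1. The planned minimum reproduces.** Overall F test in multiple regression, with noncentrality f² × N, df1 = 20 and df2 = N − 21. With f² = 0.15, alpha 0.05 and power 0.95, the smallest N is 222 (power 0.951).

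**2. The floor is safe.** If every country has at least 222, the mean is at least 222 and the cap is at least 1.1 × 222 = 244.2, or 244. Trimming to the cap cannot take a country below 222.

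**3. The trigger can miss the imbalance.** Sizes 222 and 6 × 300:
- mean = (222 + 1,800)/7 = 288.9; cap = 1.1 × 288.9 = 317.7
- no country exceeds the cap, so nobody is discarded
- 300/222 = 1.35, a 35% gap against a 10% limit

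In general, with k countries all at or below 1.1 × mean, the smallest can be as low as (k − 1.1(k − 1)) × mean. The largest-to-smallest ratio can then reach 1.1/0.4 = 2.75 for seven countries and 1.1/0.3 = 3.67 for eight.

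**4. What discarding costs when it is triggered.** Assumed sizes 222, 3 × 400, 2 × 600, 800; total 3,422, mean 488.9.

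| Reading | Cap | Discarded | Share | Remaining gap | CI widening, largest country |
|---|---|---|---|---|---|
| Original mean | 537 | 63 + 63 + 263 = 389 | 11% | 537/222 − 1 = 142% | √(800/537) = 1.22 |
| Mean recomputed until stable | 422 | 178 + 178 + 378 = 734 | 21% | 422/222 − 1 = 90% | √(800/422) = 1.38 |
| Pairwise limit enforced | 244 | 3,422 − (222 + 6 × 244) = 1,736 | 51% | 244/222 − 1 = 10% | √(800/244) = 1.81 |

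Check on the recomputed cap: after trimming, the total is 222 + 1,200 + 3 × 422 = 2,688, the mean is 384, and 1.1 × 384 = 422.4.

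**5. What larger samples would buy.** Under the same alpha, the smallest f² detectable with 95% power falls from 0.149 at 222 to 0.108 at 300, 0.080 at 400 and 0.053 at 600.

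**The case against.** The strongest defence is that not everything is done within one country. Whether vaccination is mandatory is fixed within a country, so the ANOVA that considers it needs data from several countries. The plan also collects country-level indicators and expects similar factor structures across samples. Similar sizes would stop one country dominating a joint analysis and would keep the separate results comparable in precision. This stands as far as it goes: a reader might infer that discarding has no possible use, and the documents do not support that. But the same balance can be had in the analysis without deleting data, and the plan itself argues against joint analysis.

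Other limits also stand:

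- The planned power is not breached (step 2).
- Removal is random, so hesitant parents keep their expected share and no bias arises. A fixed seed would make the draw reproducible, though it would not recover the lost data.
- Only countries above 1.1 × mean are trimmed. It would be wrong to infer that every country recruiting beyond 222 loses data; step 3 is a counterexample.
- The reference to meeting the criterion may point back to the pairwise limit, so that trimming, once triggered, continues until that limit holds. The rule then works whenever it is triggered, at the cost in the last row of the table. The trigger still misses cases such as step 3. The fair wording is that the rule does not guarantee the criterion, not that it never achieves it.

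**Conclusion.** The concern holds in a limited form. The discard rule lowers precision in the trimmed countries and brings no gain to the separate factor analyses, regressions and MANOVAs. Because the trigger is one-sided and tied to the mean, it does not guarantee the 10% limit between countries stated beside it.

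For the one assumed set of sizes, the loss is about 11% to 21% of respondents, with the largest country's intervals widened by 1.22 to 1.38, depending on which mean is meant. More even recruitment would give a smaller loss or none. The mismatch between criterion and trigger does not depend on these sizes.

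A reader might go on to infer biased estimates or power below plan. The documents support neither. This is an inefficient and ambiguous rule that is worth correcting, not a threat to the study's validity.

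**What to change.** Delete the 10% criterion and the random discarding. Keep 222 as the minimum per country and state that all eligible respondents are analysed. For the ANOVA that considers mandatory vaccination, state how unequal sizes are handled: equal country weights, or a country-level term such as a random country effect. A separate fixed effect for each country would absorb the mandatory-status factor. Inverse-variance weights would not serve the balancing purpose, because they give the larger samples more influence.

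The cost is two sentences removed and one added, with no further recruitment. The downside is that country samples will differ in size and precision, so each country's results should be reported with its own sample size and confidence intervals. The change is best made before data are seen, so that the choice of who is analysed cannot depend on results.
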